### Run-in period and follow up assessments

The use of a pre-randomisation run-in period aims to ensure the engagement and adherence of subjects and to reduce bias associated with different levels of knowledge concerning expected benefits of the intervention. Over 4 weeks there is an educational group session, where the structure of the study, the benefits of physical activity, and the accelerometry report are explained.

Follow-up assessments will be conducted by clinicians (neurologist, neuropsychologist, and exercise physiologist not involved in the intervention sessions and blinded to the arm).

### Randomisation and masking

After the 4-week run-in period, research personnel not involved in the recruitment, assessment, or intervention are responsible for managing the randomisation process using a statistical program. The randomisation sequence is generated by R software [69]. Participants are randomly assigned (1:1) to either the intervention group (IG) or to the best practice usual care group (CG), stratified by gender.

All follow-up assessments (physical, neuropsychological, and clinical diagnosis), and also the neuroradiological evaluation, are blinded to treatment allocation, as well as in the data set registry.

### Intervention

#### Usual care

All participants receive usual care according to national guidelines. The Direção Geral da Saúde (DGS) only has guidelines for the elderly and not for subjects with VCI. In these guidelines, physical activity is recommended without further specification [70]. When clinically relevant problems are identified, the doctor in charge of the patient will be contacted for subsequent guidance.

#### Experimental intervention and implementation

In the intervention group, three physical activity sessions are planned per week (two supervised and one unsupervised) conducted over 6 months. In the first 2 months, the supervised sessions have 10 min of warm-up plus 5 min active pause (balance, agility, and coordinative exercises) plus 15 min walking plus 5 min active pause (resistance exercises, 1 series of 12 repetitions, three callisthenic exercises) plus 15 min walking plus 5 min flexibility (1 series of 10 s in three different postures). The aimed intensity in these first 2 months is 12/13. Between the second and fourth months, the duration of the walking period increases, as well as the intensity (rating of perceived exertion (RPE) 13/14). The session consists of 10 min of warm-up plus 5 min active pause (balance, agility, and coordinative exercises) plus 20 min walking plus 5 min active pause (resistance exercises, 1 series of 15 repetitions, three callisthenic exercises) plus 15 min walking plus 5 min flexibility (1 series of 10 s in three different postures). Between months 4 and 6, the duration of the walking period again increases, as well as the intensity (RPE 14/15). The session consists of 10 min of warm-up plus 5 min active pause (balance, agility, and coordinative exercises) plus 25 min walking plus 5 min of aerobic functional exercises (1 series of 15 repetitions, three callisthenic dynamic exercises) plus 20 min walking plus 5 min flexibility (1 series of 10 s in three different postures).

To measure the intensity level of the physical activity, the Borg rating of perceived exertion (RPE) ranging from 6 (rest) to 20 (maximum effort) is used [71]. Perceived exertion is how hard you feel your body is working. It is based on the physical sensations a person experiences during physical activity, including increased heart rate, increased respiration or breathing rate, increased sweating, and muscle fatigue. Although this is a subjective measure, a person’s exertion rating may provide a fairly good estimate of the actual heart rate during physical activity [71].

For the unsupervised session, participants are asked to accumulate at least 3 bouts of 10 min walking during the day, with the RPE according to their training intensity phase.

Regarding the best practise usual care group, physical activity counselling is given during the educational session before the randomisation based on their accelerometry results.

#### Intervention attendance and adherence

Intervention attendance within the 6 months is recorded in log sheets at the beginning of each session by the exercise physiologist responsible for the supervised physical activity sessions. For the unsupervised physical activity session, patients are asked in the second session of each week to report whether they have performed it or not. Dropouts are registered and, whenever the subjects allow, follow-up is maintained with the same design, although the subject cancels participation in the sessions.

### Data management and safety

Data management follows the General Data Protection Regulation and the National Clinical Trial regulation (Act n° 21/2014, 16 April). Case report forms (CRFs) only include an anonymised code. Personal identification or any data leading to personal identification is not directly associated with data collection forms. The personal identification of subjects and data collection forms are stored in different locations of the leading centre, and data is only accessed by the research team.

Adverse events are registered in all scheduled appointments and reviewed by the exercise physiologist in all sessions. Adverse events are registered in the CRF. Serious adverse events are defined in the protocol as adverse events that require hospitalisation, medical interventions, or implicate significant disability, death, or are immediately life-threatening. These implicate referral to the doctor in charge, or to the emergency room if applicable. We should note that we do not expect to have relevant serious adverse effects, as the intervention follow WHO guidelines.

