## Methods/design

### Design

AFIVASC (“physical activity in vascular cognitive impairment’) is a Portuguese multi-centre, randomised parallel group trial comparing a 6-month intervention of two moderate physical activity sessions and one unsupervised moderate physical activity session per week with an additional follow-up of 6 months to evaluate its long-term impact in comparison with the current best practice usual care. The Consolidated Standards of Reporting Trials (CONSORT) statement [19] has been used as a framework for the development of our methodology (Fig. 1). To ensure adherence, a run-in period will be conducted after inclusion. This run-in period consists of a 4-week period before randomisation during which all participants are assigned to equal procedures, namely the educational session and all planned assessments. After the run-in period, participants are randomised into two parallel groups (best practice usual care group and the intervention group). The best practice usual care group will receive the standard usual care, but they are allowed to perform physical activity by self-initiative, although supervised physical intervention is not allowed. The control of the amount of physical activity per week is performed in both groups through accelerometry. We do not expect to see high levels of physical activity in the usual care group since VCI is usually associated with a reduced initiative.

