**Fig. 1 Fig1:**
[figure not shown]
Study design. MRI magnetic resonance imaging

All participants will be followed up for 12 months. Informants (usually family members) are recruited, as is usual in cognitive studies, to provide additional data since we expect the sample size to decline over time. Participants, informants, and exercise physiologists are not blinded to the treatment, but all baseline and follow-up assessments (physical, neuropsychological, and radiological) are blinded to treatment allocation. According to data protection rules, all data are anonymised. Technicians involved in statistical analysis will be blinded to treatment allocation.

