### Study outcomes

The primary outcome measure will be cognitive decline defined as a dichotomous variable (decline/no decline) through cognitive status criteria as described in the Assessments section below. The secondary outcomes are changes in neurocognitive scores of at least 1.5 standard deviation (SD) from baseline to endpoint (using *z* scores), a decline in the raw values of neuropsychological tests, in quality of life, functional and motor status, and falls.

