### Assessments

All participants attend three visits (baseline and two follow-up) consisting of clinical neuropsychological, physical, and functional observations (baseline, 6 months, and 12 months). The study schedule is shown in Fig. 2. In these visits, participants undergo the following assessments: 1) clinical and sociodemographic assessment; 2) physical activity assessment; 3) accelerometry assessment; 4) neuropsychological assessment; 5) and brain imaging (MRI scan; this only at baseline). Informants (appointed by participants as the best available person to provide information about them) are also interviewed.

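### Adverse events are reviewed at every exercise session, which only the intervention arm has, so counts of non-serious events by arm over months 0–6 would not be comparable

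*Protocol article*

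**What the plan says.** Data management and safety sets up two routes for adverse events: "Adverse events are registered in all scheduled appointments and reviewed by the exercise physiologist in all sessions".

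The two arms do not share the second route.

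- Experimental intervention and implementation: "In the intervention group, three physical activity sessions are planned per week (two supervised and one unsupervised) conducted over 6 months".
- Design, on the usual care group: "although supervised physical intervention is not allowed". The only physical-activity contact described for that group comes before allocation: "physical activity counselling is given during the educational session before the randomisation based on their accelerometry results".
- Assessments, on what both arms share: "All participants attend three visits (baseline and two follow-up"), that is, baseline, 6 months and 12 months.
- Design (text below Figure 1): "Participants, informants, and exercise physiologists are not blinded to the treatment". The follow-up assessors, by contrast, are blinded and take no part in the sessions (Run-in period and follow up assessments).

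Falls are a secondary outcome. Study outcomes ends its list with change "in quality of life, functional and motor status, and falls". The Abstract (Methods) says that secondary outcomes are evaluated at 6 and 12 months by blinded investigators.

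**The concern.** A participant who is asked about problems twice a week will report more minor events than one who is asked once after six months, even if both had the same events. Here the difference in questioning is tied to the allocated arm. It runs through unblinded staff, and the population has cognitive impairment, in which recall over six months is likely to be weaker.

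Adverse events from both arms go into the case report form, and the Data analysis section commits to CONSORT. A table of events by arm is thus a likely product. If it pools the two routes, part of any excess under exercise will reflect how events were found rather than how often they occurred. That matters for a trial whose Discussion looks ahead to wide use of the intervention in routine practice.

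**Working it through.** The article states no figure on this point, so there is nothing to reproduce. The check is a count of contacts from the stated schedule, followed by an illustration under assumed capture rates.

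**Contacts at which adverse events are elicited, by arm (1:1 allocation)**

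- Supervised sessions: 2 per week × 24 to 26 weeks = 48 to 52. The weekly unsupervised session adds no contact of its own, since it is reported at the second session of the week (Intervention attendance and adherence).
- Months 0–6, intervention: 48 to 52 sessions + 1 visit = 49 to 53.
- Months 0–6, usual care: 1 visit.
- Months 6–12: 1 visit in each arm.
- Whole 12 months after randomisation: 50 to 54 against 2.

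These are planned contacts. Actual attendance would lower the intervention count but would not bring it near 1.

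**Apparent rate ratio with no true difference**

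Let *c* be the share of non-serious events that the 6-month visit captures, relative to session review. The documents do not give *c*; 0.6 to 0.8 is an assumption. With equal true rates, the apparent ratio over months 0–6 is 1/*c*:

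- *c* = 0.8: 1/0.8 = 1.25
- *c* = 0.6: 1/0.6 = 1.67

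Over the full 12 months the effect is diluted. If the true rate is constant and both arms have capture *c* in months 6–12, the ratio is (1 + *c*)/(2*c*):

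- *c* = 0.8: 1.8/1.6 = 1.13
- *c* = 0.6: 1.6/1.2 = 1.33

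**Sensitivity to the assumption**

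Now take 95% capture in the intervention arm and 50% to 90% in usual care, again assumed. The apparent risk ratio over months 0–6 is 0.95 divided by usual-care capture:

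| Usual-care capture | Apparent risk ratio |
|---|---|
| 50% | 1.90 |
| 60% | 1.58 |
| 70% | 1.36 |
| 80% | 1.19 |
| 90% | 1.06 |

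The direction is the same throughout. The size depends almost wholly on the assumed capture.

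**The case against.** Several points on the other side have force.

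- **Falls.** A reader might infer that falls are distorted in the same way, and that a real reduction could be hidden. The article does not support this. No passage says that falls are collected through the adverse-event route, and the Abstract puts secondary outcomes at the blinded 6- and 12-month evaluations. This objection stands. All that is open is whether a fall reported at a session could find its way into the outcome.
- **No planned test.** Adverse events are not listed as an outcome, and Data analysis states no between-arm test of them. This also stands. The point therefore concerns any tabulation or comparison by arm, not a stated analysis.
- **Usual care may have other contacts.** The article does not list its scheduled appointments, and the full protocol could add calls or visits. That is possible. The 6- and 12-month visits are the only shared contacts described after randomisation, and nothing suggests contact approaching twice a week.
- **Safeguards on recall.** A reliable informant is required and is interviewed, dementia is excluded, and consent covers access to clinical records. These narrow the gap, above all for serious events. They do not close it for minor ones.
- **A false harm signal is not shown to be likely.** With 117 per arm, a true risk of 20% to 30% and the capture rates in the table above, the chance of a spurious significant excess runs from about 4% to 71%, against a nominal 2.5% in that direction. That range is too wide to call the outcome likely, and it presupposes a test that the article does not plan.

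**Conclusion.** The unequal ascertainment holds on the article's own text: adverse events have a second, frequent and unblinded route that exists in one arm only. Counts of non-serious events by arm over months 0–6 would not be comparable and would lean against exercise.

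The size cannot be derived from the document. The apparent ratio of 1.25–1.67 rests on an assumed relative capture of 60–80% and on equal true rates. It applies to the six months of intervention and is smaller over the full year. Hospitalisations and deaths should be much less affected.

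The conclusion does not extend to falls as a secondary outcome, nor to a prediction that the trial will show false harm. It assumes that usual care has no frequent between-visit contact beyond what the article describes.

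**What to change.** 1. Add a source field to each adverse event in the case report form: elicited at a visit, or reported at a session. It must be filled in as events are recorded, since source is hard to reconstruct later.
2. State that any between-arm comparison of non-serious adverse events uses only events elicited at the 6- and 12-month visits, by the blinded assessor, with the same structured question and recall window in both arms. The question is put to everyone, whether or not an event was already reported at a session.
3. Report events known only from sessions descriptively for the intervention arm, with no between-arm test.
4. Compare serious events using the clinical records of both arms, to which participants already consent (Recruitment and study setting).
5. State that falls reported at sessions do not enter the falls outcome.

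Safety monitoring at sessions stays as it is. The cost is one field and a few lines of text, with no added visits or participants. The downside is that fewer events enter the comparison. Some imbalance may also remain, because repeated questioning at sessions can help intervention participants to remember events at the visit.

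### The serious adverse event definition includes any event needing medical intervention, so minor treated events can count beside deaths and admissions and are likelier to be captured in the exercise arm

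*Protocol article*

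**What the plan says.** All the wording at issue is in the protocol article, mostly in Data management and safety.

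- **Definition.** The article presents it as the protocol's own: "Serious adverse events are defined in the protocol as adverse events" introduces the list, which runs "adverse events that require hospitalisation, medical interventions, or implicate significant disability, death, or are immediately life-threatening". Meeting any one item is enough. The medical-intervention item has no qualifier.
- **Consequence.** For events so classed: "These implicate referral to the doctor in charge, or to the emergency room if applicable".
- **Collection.** "Adverse events are registered in all scheduled appointments and reviewed by the exercise physiologist in all sessions".
- **Who has sessions.** Experimental intervention and implementation states: "In the intervention group, three physical activity sessions are planned per week (two supervised and one unsupervised) conducted over 6 months". The usual care group has no sessions.
- **Expectation.** "we do not expect to have relevant serious adverse effects, as the intervention follow WHO guidelines". No rate is given.
- **Outcomes.** Serious adverse events are not listed under Study outcomes. The secondary outcomes include "a decline in the raw values of neuropsychological tests, in quality of life, functional and motor status, and falls", and falls are the only harm-related item. Data analysis does not mention adverse events.

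**The concern.** A seriousness category should separate events with grave consequences from the rest. Four of the five criteria do so: hospitalisation, significant disability, death and immediate threat to life. The fifth asks only whether the event needed medical intervention. A site following the text could enter a treated musculoskeletal injury under the same heading as a death.

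The problem grows because capture differs by arm. Minor treated events are the kind most likely to be missed when contact is infrequent, and deaths and admissions are much less so. The loose criterion therefore admits the events most sensitive to how often participants are asked, and the design asks the two arms at very different frequencies.

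At stake is how far a reader can rely on any account of serious harm from exercise in people with vascular cognitive impairment, previous stroke or TIA. Efficacy results are not touched.

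**Working it through.** The article states no serious-event rate, margin or comparison, so there is no figure to reproduce. The check compares the passages and then illustrates with assumed rates.

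**Step 1: frequency of contact.** Two supervised sessions a week over about 26 weeks is 2 × 26 = 52 planned sessions per intervention participant. Under Assessments, both arms have visits at baseline, 6 and 12 months. A usual care participant therefore has one scheduled follow-up visit, at the end of the 6 months, where an intervention participant has that visit plus about 52 sessions.

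**Step 2: set-up of the illustration.** Planned total 280 (Sample size), allocated 1:1 (Randomisation and masking): 280 / 2 = 140 per arm. Let s be the proportion with a strictly serious event and m the proportion with a captured minor treated event, taken as independent. Both are assumptions.

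- Proportion counted as serious = 1 − (1 − s)(1 − m).
- Share counted only because of a minor event = (proportion counted − s) / proportion counted.

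**Step 3: no true difference (s equal in both arms, true risk ratio 1.00).**

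| s | m, exercise v usual care | Counted as serious | Risk ratio | Exercise-arm share counted only for a minor event |
|---|---|---|---|---|
| 5% | 5% v 5% | 9.8% v 9.8% | 1.00 | 49% |
| 5% | 15% v 15% | 19.3% v 19.3% | 1.00 | 74% |
| 5% | 5% v 2% | 9.8% v 6.9% | 1.41 | 49% |
| 5% | 10% v 5% | 14.5% v 9.8% | 1.49 | 66% |
| 5% | 10% v 2% | 14.5% v 6.9% | 2.10 | 66% |
| 5% | 15% v 5% | 19.3% v 9.8% | 1.97 | 74% |
| 3% | 10% v 2% | 12.7% v 4.9% | 2.57 | 76% |
| 10% | 5% v 2% | 14.5% v 11.8% | 1.23 | 31% |

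Worked example, fourth row: 1 − 0.95 × 0.90 = 0.145; 1 − 0.95 × 0.95 = 0.0975; 0.145 / 0.0975 = 1.49; (0.145 − 0.05) / 0.145 = 66%. This row also describes minor events occurring equally often (10% in each arm) with half of those in usual care going unrecorded. Unequal capture alone is then enough to move the ratio.

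Over s from 3% to 10% with unequal m, the risk ratio runs from 1.23 to 2.57. The share counted only for a minor event runs from 31% to 83% (the upper end at s = 3%, m = 15%). The first two rows show that a broad definition on its own creates no false difference.

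**Step 4: a true difference (s = 10% v 5%, true risk ratio 2.0), minor events added equally.** Power is the two-sided 5% normal approximation at 140 per arm, Φ[(difference − 1.96 × pooled SE) / unpooled SE].

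| m in both arms | Counted as serious | Risk ratio | Power |
|---|---|---|---|
| 0% | 10.0% v 5.0% | 2.00 | 35% |
| 5% | 14.5% v 9.8% | 1.49 | 23% |
| 10% | 19.0% v 14.5% | 1.31 | 17% |
| 20% | 28.0% v 24.0% | 1.17 | 12% |

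The risk difference shrinks only by the factor (1 − m), from 5.0 to 4.0 percentage points at m = 20%. The dilution lies mainly in the ratio and in precision.

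**The case against.** Several objections have force and limit the point.

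**No comparison of serious events is planned.** A reader might infer that the trial's serious-harm comparison is distorted. The article describes no such table or test, so a chance of a significant excess is not a property of this plan. The power figures above only show loss of information. What stands is conditional: any tabulation by arm would inherit the problem.

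**A broad definition does not by itself bias anything.** This is correct, as the equal-rate rows show. The asymmetry has to come from unequal occurrence or unequal capture. Unequal capture is likely from the article's own arrangements, but its extent is unknown.

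**The text says the event must require intervention.** That is narrower than an event that merely received some treatment, and the article does not say how a dressed graze or a strain given an analgesic would be classed. A reader should not infer that sites must count every such event. They can, because nothing in the wording draws the line.

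**The expectation of no serious effects is not a clear contradiction.** It is tempting to read "we do not expect to have relevant serious adverse effects, as the intervention follow WHO guidelines" as incompatible with the definition. It concerns relevant effects of the intervention, not all events, so unrelated treated illness does not contradict it.

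**The article condenses a fuller protocol,** which may carry a qualifier. That is possible. But the article does not leave the matter open: it states a definition and attributes it to the protocol. If the full text differs, the published wording misstates it and still needs correcting.

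**Conclusion.** The point holds in limited form. As stated, the definition lets an event that needed only medical treatment count as serious, and session-by-session review in one arm makes such events likelier to be recorded there. A tabulation of serious events by arm could be diluted or could show a spurious excess against exercise.

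Neither the size nor the net direction can be determined from the article. The ranges shown rest on assumed rates, on independence of minor and serious events, and on 140 per arm. If minor events occur and are captured equally, the null ratio stays at 1.00 and only dilution remains.

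This is a modest defect in harm reporting that is worth correcting. It does not affect the primary outcome, the sample size or the type I error.

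**What to change.** 1. Reconcile the published definition with the full protocol. For reporting, limit the medical-intervention criterion to interventions needed to prevent one of the other listed serious outcomes.
2. Add a field to the adverse event form recording which criterion or criteria each serious event met.
3. Tabulate serious events by arm and criterion. Show death, hospitalisation, significant disability and life-threatening events separately from events that met only the medical-intervention criterion. Unequal capture will remain, but its effect will be largely confined to a row where the reader can see it.
4. Leave the referral pathway in Data management and safety unchanged. The same definition triggers referral, so the reporting change must not remove referrals that the current wording provides.

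The cost is one clarified sentence, one form field, and reclassification of any events already logged. Reclassification should be blind to arm, so mentions of exercise sessions need removing from the event descriptions first. The article does not say whether the existing forms hold enough detail; where they do not, the criterion should be reported as not recoverable.
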